### Data analysis

#### Sample size calculation

Nowadays, there is 33% 30-day morbidity and 3.8% 30-day mortality in patients undergoing colorectal surgery in the Netherlands [3, 78]. We expect the high-risk group (patients with a VAT < 11 mL/kg/min) to have a morbidity rate of 50%. Dunne et al. stated that a 10% improvement in cardiorespiratory fitness would move 30% of the patients from high to low operative risk [25, 28]. Robinson et al. [34] showed that 21% of the non-frail colorectal patients had a postoperative complication, versus 40% in the pre-frail group and 58% in frail patients. We hypothesized a complication rate of 20% in the prehabilitation group.

For the sample size calculation we used the computer program PS Power and Sample Size Calculations version 3.0, January 2009 (Copyright © 1997-2009 by William D. Dupont and Walton D. Plummer) [79, 80]. Using an alpha of 0.0492 (due to one interim analysis) and a power of 0.80, we need 39 patients in each group to find statistically significant results. Taking into account 10% dropout, we need 43 patients in each group.

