#### Statistical analysis

Nominal variables will be presented as numbers with percentages. Continuous variables will be presented as mean ± SD, or as median and interquartile range, as appropriate. Data will be presented in tables and figures. All tests will be performed on the intention to treat population, and on the per-protocol population. Data distribution will be checked with help of an epidemiologist.

For categorical variables, chi-squared tests or Fisher’s Exact tests, as appropriate, will be performed to analyze the difference between the intervention and control group. For continuous variables this will be done by independent samples t-tests or Mann-Whitney U tests, as appropriate. A repeated measurements analysis (mixed models in SPSS) will be performed to assess changes over time in continuous variables. A cost-effectiveness analysis will be performed, with the use of quality adjusted life years. Withdrawn patients will be followed by checking the patient’s data file. We will use the intention-to-treat analysis to avoid various misleading artifacts.

When half of the patients needed that are calculated (43 patients) are included, a blinded independent data analyst will perform an interim analysis with a stopping rule according to O’Brien-Fleming [81]. If this interim analysis shows a significant difference in postoperative complications between the prehabilitation group and the usual care group (at *P* < 0.0054), this data analyst will contact the Medical Ethics Committee, and debate the outcome of the interim analysis and its eventual repercussions. Thereupon this committee will advise the principle investigator of the research team (JK) to decide to stop the inclusion in case of superiority. If the interim analysis shows no or minimal difference (< 10% on overall complications), the study will be stopped due to futility. Because of the interim analysis, the final *P*-value that is considered to be significant is reduced to *P* < 0.0492.

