
We believe that preoperative exercise training in patients ‘merely’ undergoing elective colorectal resection will be only cost-effective and sustainably implementable in usual care pathways when performed in high-risk patients (those with a low cardiorespiratory fitness, e.g., a VAT < 11 mL/kg/min). Hence, an adequate preoperative risk stratification protocol, such as the protocol used in the current study (a CPET for patients with a VSAQ score < 7 METs, of which those patients with a VAT < 11 mL/kg/min at the CPET will be eligible for and advised to participate in prehabilitation), will probably lead to a feasible sustainable implementation of the prehabilitation concept. For patients undergoing elective colorectal resection and (neo)adjuvant chemotherapy and/or radiotherapy, prehabilitation might be cost-effective in all patients. Cost-effectiveness should be expected, and therefore evaluated, in terms of, among other things, fewer postoperative complications, fewer reoperations, less intense clinical care, a shorter length of stay, a more effective surgical planning (process-optimization), fewer readmissions, less intense rehabilitation, shorter rehabilitation period, and earlier resumption of work.

The strengths of our present study are the selection of high-risk patients, the clear description of the study design and prehabilitation program, the 1:1 randomization between the prehabilitation and usual care group, the use of validated measurement instruments, and the adjustment of the physical exercise training program to the cardiorespiratory fitness of the individual patient based upon the results of the CPET. Moreover, prehabilitation will be performed in a community physical therapy practice in the catchment of the patient’s home. In this way we will try to reach the frailest patients who are not capable to visit the hospital each time.

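### The binding interim futility rule (stop if the difference is below 10%) has no sign, does not say whether 10% is absolute or relative, and is not counted in the stated 80% power

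*Protocol article*

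**What the plan says.** All references are to the protocol article.

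- **Sample size calculation.** The expected usual care rate is 50% ("We expect the high-risk group (patients with a VAT < 11 mL/kg/min) to have a morbidity rate of 50"), and for the other arm: "We hypothesized a complication rate of 20% in the prehabilitation group". Then: "Using an alpha of 0.0492 (due to one interim analysis) and a power of 0.80, we need 39 patients in each group", and "Taking into account 10% dropout, we need 43 patients in each group". The reduced alpha is the only stated allowance for the interim analysis.
- **Statistical analysis, timing.** "When half of the patients needed that are calculated (43 patients) are included", a blinded independent analyst performs one interim analysis. With "the 1:1 randomization between the prehabilitation and usual care group" (Discussion), that is 21 or 22 patients per arm.
- **Statistical analysis, efficacy branch.** A significant difference between prehabilitation and "usual care group (at *P* < 0.0054") is taken to the ethics committee. The committee then advises on stopping inclusion if there is superiority.
- **Statistical analysis, futility branch.** "If the interim analysis shows no or minimal difference (< 10% on overall complications), the study will be stopped due to futility". No reason is given for the cut-off.

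**The concern.** Three features of the futility sentence are open to criticism.

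1. **No direction.** A difference without a sign is small only when the arms are close. An excess of complications of 10 points or more under prehabilitation is not a small difference, so the literal rule lets that trial continue. The efficacy branch speaks of stopping only for superiority, so neither branch provides a stop for that result.
2. **Unclear scale.** On a usual care rate of 50%, 10% absolute is 10 points, while 10% relative is 0.10 × 50 = 5 points. The stopping zone differs by a factor of two.
3. **Not in the power.** The efficacy result leads to discussion and advice, but the futility result leads to a mandatory stop. A mandatory futility stop can only lower power, and the sample size section does not mention it.

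At stake are an unambiguous instruction to the interim analyst, and a power figure that describes the design as it will be run.

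**Working it through.** **Inputs** (Sample size calculation and Statistical analysis): 50% vs 20%; final P < 0.0492; interim P < 0.0054; interim at 43 of 86 patients; 39 evaluable or 43 randomised per arm; 1:1 allocation. Assumptions: two-sided Pearson chi-squared test without continuity correction; 10% read as absolute points; efficacy counted only in favour of prehabilitation.

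**Step 1: reproduce the plan's 39.** The mean rate is 0.35.

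n = [z(0.9754)·√(2·0.35·0.65) + z(0.80)·√(0.5·0.5 + 0.2·0.8)]² / 0.30²
= [1.967·0.6745 + 0.8416·0.6403]² / 0.09 = 38.7, so 39 per arm.

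The dropout allowance is 39 × 1.1 = 42.9, so 43. The fixed-sample formula gives 39 exactly, so the futility rule was not counted.

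**Step 2: precision at the interim.** With 22 and 21 patients the standard error under the design is √(0.25/22 + 0.16/21) = 0.138, about 14 points. Results of 9/21 vs 7/21 differ by 9.5 points with a standard error of 14.9, giving a 95% interval of about −20 to +39 points, which includes 30. With 22 per arm, a two-event advantage (2/22 = 9.1 points) stops the trial and a three-event advantage (3/22 = 13.6 points) does not.

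**Step 3: exact two-stage enumeration.** Every pair of interim counts is weighted by its binomial probability. The trial succeeds at the interim, stops for futility, or goes on to the final test. Splits are usual care vs prehabilitation. Futility stops are shown for the unsigned and then the signed reading.

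| Interim split | Final per arm | Power without rule | Power with rule | Futility stop, 50% vs 20% | Mean conditional power if stopped | No effect: excess of 10 points or more under prehabilitation |
|---|---|---|---|---|---|---|
| 20 vs 19 | 39 | 80.4% | 77.6% | 9.3 / 9.7% | 30% | 26% |
| 19 vs 20 | 39 | 80.4% | 78.4% | 7.7 / 7.9% | 27% | 26% |
| 22 vs 21 | 39 | 80.4% | 78.7% | 7.2 / 7.6% | 22% | 27% |
| 20 vs 20 | 39 | 80.4% | 79.1% | 5.5 / 6.0% | 23% | 32% |
| 21 vs 22 | 39 | 80.4% | 79.2% | 6.0 / 6.2% | 20% | 27% |
| 22 vs 21 | 43 | 85.4% | 82.8% | 7.2 / 7.6% | 36% | 27% |
| 21 vs 22 | 43 | 85.4% | 83.5% | 6.0 / 6.2% | 33% | 27% |
| 22 vs 22 | 43 | 85.4% | 82.2% | 8.6 / 8.7% | 37% | 23% |

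The loss is the stop probability times the mean conditional power. In the first row, 9.3% × 30% = 2.8 points. With exactly 20 per arm, a two-event difference is exactly 10 points and does not meet the rule, which explains the 32%.

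**Step 4: conditional power within the stopping zone.** This assumes a true 50% vs 20%. At 22 of 43 per arm it is 23% at zero difference, 35% at one event and 48% at two events. At 20 vs 19 of 39 it is 37–51% for differences of about 7 to 9.5 points. A normal approximation just under 10 points gives about 47% (39 per arm) and 52–53% (43 per arm). So it is roughly 35–55% near the cut-off and falls quickly below it. If the observed trend is assumed to continue instead, it is about 2–8% at the cut-off.

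**Step 5: what the sign changes.** Under the design effect, the signed and unsigned readings differ in power by no more than about 0.02 points. Under no effect (50% in both arms), the signed rule stops 73–77% of trials (68% with 20 per arm) and the unsigned rule 46–55% (36%).

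**The case against.** The strongest defence has four parts.

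- **The intended direction is clear from context.** The primary hypothesis is that prehabilitation reduces complications, so a minimal difference can be read as an insufficient reduction, which would include harm. That reading is reasonable, but the sentence does not say it, and a binding rule should not depend on it. A reader might infer that the plan deliberately continues a trial that trends towards harm. The documents do not support that: the gap is one of wording, any difference significant at the interim threshold goes to the ethics committee, and adverse events are recorded.
- **The analyst must already know direction.** Judging superiority requires it, so one cannot conclude from the blinding that direction is hidden. What stands is that the article does not say how a blinded analyst learns which arm is which.
- **The cut-off is not reckless.** A reader might infer that the rule generally abandons trials with a 40–50% chance of success. That holds only near the cut-off and only if the full 30-point effect is real. The mean over stopped trials is about 22–37%, and about 7–12% if the true prehabilitation rate is 30%.
- **The power loss is small.** It is about 1–3 points, in a calculation that rests on assumed rates. A reader might infer that 80% power is not delivered. At 39 evaluable per arm it falls slightly short. However, 43 per arm are planned, analysis is by intention to treat, and withdrawn patients are followed through their records, so power could be as high as 82–83.5%.

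**Conclusion.** The point holds as a should-fix. The futility rule is binding, unsigned, unclear on scale and absent from the power calculation. Read literally, it treats a small benefit more harshly than a 10-point or larger excess of complications, which would arise in about 23–27% of trials under no effect (32% with exactly 20 per arm). Counting the rule, power at 39 evaluable per arm is 77.6–78.7% for three of the five splits examined and about 79% for the other two, against 80.4%. At 43 per arm without dropout it is 82–83.5%, against 85.4%. About 6–10% of trials stop for futility under the design effect.

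These figures assume 50% vs 20%, an absolute 10 points, and the chi-squared test. The article also allows Fisher's exact test. With that test, power without the rule is already about 73% (39 per arm) or 79% (43 per arm), and the rule takes off a further 1–2 points. The calculation supports clarifying the rule and restating the power. It does not show a serious loss of power or that the cut-off must move.

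**What to change.** 1. State the rule as a signed absolute difference, usual care rate minus prehabilitation rate, in percentage points, so that a result against prehabilitation also meets it.
2. Say that the interim analyst is told which coded arm is prehabilitation.
3. Report the power with the rule included, at 39 evaluable and at 43 per arm.

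This takes one amended paragraph. Adding the sign costs practically no power (Step 5).

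**Optional, as a trade-off for the sponsor:** make the rule non-binding, or stop only if the prehabilitation rate is not numerically lower than the usual care rate. The second choice gives 80.0–80.3% power at 39 per arm. The price is that, under no effect, about 50% of trials stop early (about 56% with equal interim arms, because ties count) instead of about 73–77% under the signed 10-point rule, so more trials without an effect run to 86 patients. Either choice can be defended if the reason is stated.

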## Discussion

Surgery is an important treatment modality in patients with colorectal cancer. Unfortunately, over 30% of patients develop a postoperative complication after elective colorectal resection [3]. Older patients, especially frail patients, with a poor cardiorespiratory fitness are more prone to postoperative complications and require specific preoperative risk stratification. Optimizing preoperative physical fitness (e.g., cardiorespiratory fitness, muscle strength, and functional mobility) through prehabilitation may improve postoperative outcomes in patients undergoing major abdominal surgery [6]. Currently, there is a lack of information in the literature about the effect of preoperative exercise training on overall postoperative complications in high-risk older patients with colorectal cancer. Most of the studies so far were rather underpowered, heterogeneous, and biased toward selection of patients with low risk of postoperative complications [6, 29, 30]. The primary aim of our current randomized controlled trial is to measure the effect of a three-week prehabilitation program on postoperative complications in patients with a poor cardiorespiratory fitness, as indicated by a VAT < 11 mL/kg/min, who will undergo elective colorectal resection for colorectal cancer or dysplasia grade I,II, or III.

Postoperative complications can extend length of hospital stay, and may lead to repeated hospital admissions, chronic ill health, and a decrease or even permanent loss in functional capacity and health-related quality of life [6]. Patients with a higher cardiorespiratory fitness might be more resilient to cope with the stress associated with major abdominal surgery, with subsequent better postoperative outcomes. Optimizing preoperative cardiorespiratory fitness may therefore not only decrease postoperative complications, but may also decrease associated hospital costs, enhance the patient’s quality of life, and promote independent functioning in daily life. Our intervention fits well with the ‘prevention of limitations to function’ view in the elderly, of the Health Council of the Netherlands [82], as well as with the recently proposed new schemes of the international classification of functioning, disability, and health (ICF) to promote functioning and health [83].

According to the Dutch guidelines, patients will ideally be operated within five weeks from time of pathologic-anatomic diagnosis, and at latest within seven weeks [3]. The period between the decision for surgery and the actual surgery is limited, and therefore the valuable available time for prehabilitation is short. Moreover, some patients experience (severe) complaints of their illness, and therefore resection cannot be postponed for several weeks. However, given the need for prehabilitation interventions to be both effective and time-efficient, Weston et al. [84] indicated that carefully designed and supervised high-intensity interval training programs might be a promising perioperative strategy for enhancing cardiorespiratory fitness within a short period.

The present study, like all studies do, bares some limitations. Firstly, merely patients in the prehabilitation group will perform a second CPET to investigate the effect of the prehabilitation program on cardiorespiratory fitness. Consequently, we are not able to investigate the changes in cardiorespiratory fitness in the preoperative waiting period in the usual care group. However, the waiting period in patients in the usual care group was kept as short as possible to prevent these patients to improve their level of fitness by organizing their own preoperative exercise training program. Moreover, a study in patients planned for elective hepatic resection for colorectal liver metastases reported no significant differences in CPET variables in the control group after a four-week waiting period [25]. Secondly, the prehabilitation program in the present study consists only of a preoperative exercise training program, while it was recently indicated that studies evaluating a prehabilitation program combined with a nutritional intervention before elective major surgery in adults are producing encouraging early results [31]. However, definitive clinical evidence of physical and nutritional prehabilitation is currently very limited [31, 85, 86]. Thirdly, up till now, patient inclusion appears to be challenging. Not all patients are able and/or willing to attend the prehabilitation program due to personal, logistical, and time limitations (e.g., restricted time availability between the first outpatient visit and surgery, living too far away from the community physical therapy practice, and/or no traveling opportunities, planned vacation prior to surgery, not interested in participation). Moreover, at the start of the present study patients in both groups were informed about the possible effects of prehabilitation. We experienced that some patients in the usual care group initiated preoperative physical exercise training themselves, possibly resulting in the risk that we will not be able to detect a difference between the prehabilitation and usual care group. Therefore, we made an amendment to the study protocol (approved in April 2016 by the Medical Ethics Committee Twente) in which patients in the prehabilitation group and the usual care group will be informed differently. The patients in the usual care group will not receive information about the possible effects of prehabilitation and their elective colorectal resection was planned at the earliest convenience. Fourthly, in the present study a geriatric assessment will be completed at baseline only. Baseline data as predictors of postoperative outcome may be confounded by the effect of the prehabilitation program. Therefore, only data from patients in the usual care group will be used to investigate the value of a limited geriatric assessment to perform preoperative risk stratification. However, the power for this secondary objective might be inadequate, as the sample size calculation was not based on this objective.

We believe that preoperative exercise training in patients ‘merely’ undergoing elective colorectal resection will be only cost-effective and sustainably implementable in usual care pathways when performed in high-risk patients (those with a low cardiorespiratory fitness, e.g., a VAT < 11 mL/kg/min). Hence, an adequate preoperative risk stratification protocol, such as the protocol used in the current study (a CPET for patients with a VSAQ score < 7 METs, of which those patients with a VAT < 11 mL/kg/min at the CPET will be eligible for and advised to participate in prehabilitation), will probably lead to a feasible sustainable implementation of the prehabilitation concept. For patients undergoing elective colorectal resection and (neo)adjuvant chemotherapy and/or radiotherapy, prehabilitation might be cost-effective in all patients. Cost-effectiveness should be expected, and therefore evaluated, in terms of, among other things, fewer postoperative complications, fewer reoperations, less intense clinical care, a shorter length of stay, a more effective surgical planning (process-optimization), fewer readmissions, less intense rehabilitation, shorter rehabilitation period, and earlier resumption of work.

The strengths of our present study are the selection of high-risk patients, the clear description of the study design and prehabilitation program, the 1:1 randomization between the prehabilitation and usual care group, the use of validated measurement instruments, and the adjustment of the physical exercise training program to the cardiorespiratory fitness of the individual patient based upon the results of the CPET. Moreover, prehabilitation will be performed in a community physical therapy practice in the catchment of the patient’s home. In this way we will try to reach the frailest patients who are not capable to visit the hospital each time.

## Abbreviations

ASA: American Society of Anesthesiologists
CPET: Cardiopulmonary exercise test
EORTC QLQ-C30: Quality of life questionnaire of the European organization for research and treatment of cancer
EQ-5D: EuroQol 5D
GDS 15: Geriatric Depression Scale 15
GFI: Groningen Frailty Indicator
IADL: Instrumental activities of daily living
MET: Metabolic equivalent of task
SNAQ: Short nutritional assessment questionnaire
TUG: Timed up-and-go
VAT: Ventilatory anaerobic threshold
WHO: World Health Organization
